### Randomisation

Following completion of baseline testing, participants will be randomly allocated (1:1 ratio) to either the UC or Ex + SED group by an independent researcher via a computer-generated random number sequence. Stratified permuted blocked randomisation will be used with participants stratified by transplant conditioning intensity (myeloablative or reduced intensity conditioning) and sex (male or female). Information relating to the allocation sequence will be kept on a separate, password protected database accessible only to the independent researcher and principle investigator.

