### Sample size calculation

No prior studies have directly assessed the effect of a structured exercise intervention on changes in VO_2_peak and cardiac output in this patient cohort. As such, we based our sample size calculations on data collected from our group’s previously published work that utilised a similar exercise intervention in women being treated for breast cancer [74], whereby clinically meaningful changes in cardiorespiratory fitness and cardiac function were observed. The present study is powered to detect a minimum between-group difference in VO_2_peak of 10% (SD = 11%, effect size = 0.91) and cardiac output of 9% (SD = 10%, effect size = 0.9) after treatment, assuming a conservative correlation coefficient of *r* = 0.4 between baseline and follow-up testing. To detect this difference 20 completions per group are required (80% power; alpha = 0.025; multiple primary endpoints). To account for withdrawals, mortality associated with disease progression and treatment, and uncertainty related to the COVID-19 pandemic, a total of 60 participants will be recruited (Ex + SED; *n* = 30 and UC; *n* = 30).

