### Statistical analyses

To examine the differential effects of the intervention on VO_2_peak, peak cardiac output, and additional secondary and exploratory outcome measures, generalised linear mixed modelling will be conducted (adjusted for baseline values) with participants as the random effect, time as the repeated measures factor, and group and group-by-time interactions as the fixed effects. The covariance structure of the model will be informed by the Akaike information criteria. The primary analysis will be conducted on an intention-to-treat basis and a probability level of 0.025 will be adopted to account for multiple primary outcome endpoints. Standardised effect sizes (Cohen’s *d*) will be calculated to determine the magnitude of change for within and between group effects. A per protocol analysis including participants who completed > 66% of the planned exercise sessions will also be performed.

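### The model omits both stratification factors, which gives up some precision if they predict the 12-week outcome beyond baseline

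*Protocol article*

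**What the plan says.** In the Randomisation section of the protocol article, "participants will be randomly allocated (1:1 ratio") and "Stratified permuted blocked randomisation will be used", with "participants stratified by transplant conditioning intensity (myeloablative or reduced intensity conditioning) and sex (male or female"). That makes four strata. The block size is not given.

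Under Statistical analyses, "generalised linear mixed modelling will be conducted (adjusted for baseline values"), with participant as the random effect and "time as the repeated measures factor, and group and group-by-time interactions as the fixed effects". The baseline value is the only covariate named. Neither conditioning intensity nor sex appears, and no other section of the article adds them.

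Under Sample size calculation, the trial is sized on a "minimum between-group difference in VO_2_peak of 10% (SD = 11%, effect size = 0.91") and "cardiac output of 9% (SD = 10%, effect size = 0.9"), "assuming a conservative correlation coefficient of *r* = 0.4 between baseline and follow-up testing". The calculation takes no credit for the strata.

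**The concern.** Stratified blocks keep the arms close to balanced on conditioning intensity and sex, so these factors contribute little to chance differences between arms. A model without them still counts whatever variance they explain as residual error. If they are prognostic given baseline, the reported standard error exceeds the true variability of the treatment estimate. The test then rejects less often than its nominal level, and the intervals are wider than they need to be.

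The condition is most plausible for conditioning intensity. The Background says that reduced-intensity regimens carry less cardiac toxicity, and both primary outcomes are cardiovascular. Baseline testing is about two weeks before admission. Table 2 read with the phase 1 text places the transplant about a week into the stay. Conditioning toxicity therefore arises after the baseline test, and adjusting for baseline cannot absorb it. The case for sex is weaker: a sex difference in VO2peak or cardiac output is already present at baseline and should be largely absorbed there.

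What is at stake is efficiency in a small trial that plans for as few as 20 completers per arm.

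**Working it through.** **Inputs from the protocol article.** VO2peak difference 10% with SD 11% (d = 10/11 = 0.909); cardiac output difference 9% with SD 10% (d = 0.90); r = 0.4; alpha 0.025 per endpoint; power 80%; 20 completers per group; 60 recruited. Table 3 measures both primary outcomes only at baseline and 12 weeks, so the mixed model is in effect an analysis of covariance on one follow-up value.

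**Assumptions.** A two-sided test (sidedness is not stated), blocks of 4, losses at random, and R2, the share of residual variance after baseline that the two factors explain. The documents give no R2, so 0% to 20% is shown.

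**Step 1: the plan's own figure.** n per group = 2(z_0.9875 + z_0.80)^2 (1 - r^2)/d^2, with (2.241 + 0.842)^2 = 9.505.
- VO2peak: 2 × 9.505 × 0.84/0.826 = 19.3, so 20.
- Cardiac output: 2 × 9.505 × 0.84/0.81 = 19.7, so 20.

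The stated 20 per group is reproduced from the baseline correlation alone. The t-based versions give 21 and 22.

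**Step 2: full balance, analytic.** The model standard error is too large by the factor 1/sqrt(1 - R2). The actual type I error is then 2[1 - Phi(2.241/sqrt(1 - R2))]. VO2peak power at 20 per group comes from the noncentral t with d = 0.909/sqrt(0.84(1 - R2)), on 35 df with the factors in the model. The model with baseline only, with R2 = 0 and 37 df, gives 78.5%.

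| R2 | SE factor | Type I error as written | Power with factors |
|---|---|---|---|
| 5% | 1.026 | 2.15% | 80.5% |
| 10% | 1.054 | 1.81% | 82.8% |
| 20% | 1.118 | 1.22% | 87.2% |

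**Step 3: allow for losses.** Blocks balance the 60 randomised, not the 40 who may complete. Stratified blocks were simulated with 60 randomised and either a random 40 or all 60 analysed (6,000 runs per setting). VO2peak power, model as written versus model with both factors:

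| R2 | 40 analysed | 60 analysed |
|---|---|---|
| 0% | 77.4% vs 76.1% | 92.4% vs 92.1% |
| 5% | 77.6% vs 78.0% | 93.9% vs 94.7% |
| 10% | 77.4% vs 80.6% | 94.1% vs 95.3% |
| 20% | 78.1% vs 84.7% | 94.5% vs 97.0% |

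Repeat runs agree to within about 1 point of power.

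At R2 = 20% with 40 analysed, the mean model standard error is 0.294 against an actual SD of the estimate of 0.280. That is about 5% too large (0.294/0.280 = 1.05), not the 12% seen under full balance. The type I error of the model as written at R2 = 20% was 1.8% with 40 analysed and 1.2% with all 60. The simulation error is about 0.2 points (sqrt(0.018 × 0.982/6000) = 0.0017), and repeat runs differ by a few tenths of a point.

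**The case against.** The strongest objection is that the loss is conditional and may be small. If the factors add nothing beyond baseline, nothing is lost, and including them costs about 1 point of power at 40 completers. At 5% explained variance the gain is within simulation error. The Background also says that reduced-intensity conditioning brings more relapse and graft-versus-host disease, so its net effect on fitness could partly cancel. All of this stands, and it is why the point is worded conditionally.

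A reader might infer three stronger claims that the documents do not support:
- **That the standard errors are certainly too large.** This needs a prognostic strength that the documents do not give, and for sex the argument is weak after baseline adjustment.
- **That the planned sample size fails.** It does not: the 20 per group was derived without the strata. Twenty is also the floor; with all 60 analysed, power for the model as written is above 92% throughout.
- **That the full-balance figures, such as a 1.2% type I error at 20%, apply to 40 completers.** The planned allowance for losing one third (10 of 30 per arm) loosens the balance, and the effect is smaller.

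It can also be said that a condensed article may leave covariates to a fuller plan. That lowers the weight of the point but does not remove it: the article does list the model's terms and names one adjustment variable without the two used in the randomisation.

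**Conclusion.** The mismatch between the stratified randomisation and the stated model is real, and the model would be better with both factors. The consequence is forgone efficiency and a conservative test; the treatment estimate is not biased and false positives do not increase.

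If the factors explain 10% to 20% of the residual variance, adjustment is worth about 3 to 7 points of VO2peak power with 40 analysed, and about 1 to 3 points with all 60. If they explain nothing, it costs about 1 point at 40. At 20%, the type I error of the model as written is about 1.7% to 1.9% with 40 analysed and about 1.2% with 60, against the nominal 2.5%.

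These sizes rest on assumed prognostic strength, blocks of 4, a two-sided test and losses at random. The change is worth making because the plausible gain exceeds the worst-case cost, but the validity of the trial does not depend on it.

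**What to change.** In Statistical analyses, add conditioning intensity (myeloablative or reduced) and sex, with the values recorded at randomisation, as fixed covariates in the models for VO2peak and peak cardiac output and in the other continuous-outcome models. Functional independence is binary and should be considered separately, because covariate adjustment there can change which odds ratio is estimated.

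Make the change before outcome data are seen by arm, so that the covariates are not chosen after the fact. The cost is one line of text and two degrees of freedom, with at worst about 1 point of power if the factors turn out not to be prognostic. The sample size needs no change.

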Beyond the promotion of purposeful exercise, the reduction and interruption of prolonged periods of time spent sitting or reclining has emerged as an important health target. This is based on the evidence that time spent sedentary poses risks to cardiovascular health that are additional to those of lack of physical activity [43–45]. In the context of allo-SCT, the necessary confinement to a hospital room (~ 3–5 weeks) generally coincides with a marked increase in what is considered an extreme form of sedentary behaviour—bedrest. Thus, a multi-faceted intervention that aims to both increase purposeful exercise and interrupt prolonged periods of sedentary time through replacement with light exercise might be the ideal therapeutic tool to counteract the negative cardiovascular consequences associated with physical deconditioning, cancer therapies, and the pathological perturbations of allografting. Indeed, evidence suggests that structured aerobic and resistance exercise, combined with a reduction in sedentary time, has the potential to have widespread effects on important cardiovascular organs including the heart [46–49], skeletal muscle [50–54], vasculature [47, 55, 56], and blood cells [49], as well as exerting systemic effects that favourably impact these organs [52, 57–60]. No studies have investigated the efficacy of a multi-faceted exercise intervention in preserving cardiovascular function, improving quality of life, and reducing symptoms of fatigue in patients undergoing allo-SCT.

Therefore, in a two-arm randomised controlled trial, the ALLO-Active study will evaluate the efficacy of a ~ 4 month multi-faceted exercise intervention—commenced upon admission for allo-SCT—in preserving cardiovascular function (assessed as VO_2_peak and peak exercise cardiac output; primary endpoints) and improving quality of life, fatigue, and functional independence (VO_2_peak ≥ 18 ml.kg^−1^.min^−1^; secondary endpoints) compared to a usual clinical care control. The intervention is designed to increase purposeful aerobic and resistance exercise and reduce sedentary time through replacement with light exercise and we hypothesise that it will:1. Attenuate the decline in VO_2_peak and peak exercise cardiac output as compared with usual care.2. Improve quality of life, reduce symptoms of fatigue, and improve functional independence compared with usual care.

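### Testing each primary outcome at a fixed 0.025 is valid, but Holm's procedure has the same family-wise error and makes it likelier that both are supported

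*Protocol article*

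**What the plan says.** Under Statistical analyses, the primary analysis is by intention to treat and "a probability level of 0.025 will be adopted to account for multiple primary outcome endpoints". The Methods part of the Abstract gives the same threshold for both outcomes. Neither place has a step-down, hierarchical or alpha-recycling rule, so each outcome is tested at 0.025 whatever the result for the other.

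The Sample size calculation is built on that level. It takes a "between-group difference in VO_2_peak of 10% (SD = 11%, effect size = 0.91") and "cardiac output of 9% (SD = 10%, effect size = 0.9) after treatment", with a correlation of "0.4 between baseline and follow-up testing", and concludes that "20 completions per group are required (80% power; alpha = 0.025; multiple primary endpoints"). Allowing for losses, "a total of 60 participants will be recruited", 30 per arm.

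The first hypothesis, at the end of the Background, names the two outcomes together: "Attenuate the decline in VO_2_peak and peak exercise cardiac output as compared with usual care".

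**The concern.** Once one outcome has met 0.025, the fixed rule still holds the other to 0.025. Family-wise control at 0.05 does not require this. If VO2peak succeeded and peak cardiac output gave p = 0.03, the plan would report cardiac output as not shown, whereas Holm would count it as shown within the same family-wise 0.05.

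The second result matters here. Hypothesis 1 covers both outcomes, and the Background says it is unknown how far any benefit is cardiac rather than peripheral, which the cardiac output result helps to answer. The trial is also small by its own account (Practical challenges, strengths, and limitations), so power available without extra patients is worth having.

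**Working it through.** **Inputs from the Sample size calculation.** d1 = 10/11 = 0.909 (VO2peak); d2 = 9/10 = 0.90 (cardiac output); baseline to follow-up correlation r = 0.4; alpha 0.025 per outcome; power 80%; 20 completers per arm. Allocation is 1:1 (Randomisation).

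**Assumptions.** Sidedness is not stated; I take two-sided. The correlation rho between the two outcomes is not stated; I use 0 to 0.9.

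**1. The plan's own figure.** For a baseline-adjusted comparison, n per arm = 2(z₀.₉₈₇₅ + z₀.₈₀)²(1 − r²)/d².

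- Common part: 2 × (2.241 + 0.842)² × 0.84 = 15.97.
- VO2peak: 15.97/0.826 = 19.3, so 20.
- Cardiac output: 15.97/0.81 = 19.7, so 20.

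The stated 20 per group is reproduced. An unadjusted one-sided test at 0.025 gives 19 and 20, so this agreement does not prove that two-sided tests were meant. The two-sided reading is the one that uses the stated r.

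**2. Error control under Holm.** If both nulls are true, a false claim needs at least one p-value below 0.025, which has probability at most 0.025 + 0.025 = 0.05. If one null is true, a false claim needs that p-value below 0.05, which has probability at most 0.05. Neither step uses the correlation.

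**3. Chance of supporting both, by hand (normal approximation, 20 per arm, rho = 0).** The noncentralities are d/√0.84 × √10 = 3.137 and 3.105.

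- Power at 0.025: 0.815 and 0.806.
- Power at 0.05: Φ(3.137 − 1.960) = 0.880 and Φ(3.105 − 1.960) = 0.874.
- Fixed rule: 0.815 × 0.806 = 0.657.
- Holm: 0.815 × 0.874 + 0.880 × 0.806 − 0.815 × 0.806 = 0.765.
- Gain: 10.8 points. The same approximation gives 8.9 at rho = 0.5 and 6.3 at rho = 0.9.

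**4. The same with t statistics.** This suits the trial's size better. Simulation with 2n − 3 degrees of freedom (37 at n = 20):

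| Completers per arm | rho | Both, fixed 0.025 | Both, Holm | Gain (points) |
|---|---|---|---|---|
| 20 | 0 | 61% | 73% | 12 |
| 20 | 0.5 | 66% | 76% | 10 |
| 20 | 0.7 | 68% | 78% | 9 |
| 20 | 0.9 | 73% | 80% | 7 |
| 25 | 0 to 0.9 | 77% to 84% | 86% to 89% | 9 to 5 |
| 30 | 0 to 0.9 | 87% to 91% | 93% to 94% | 6 to 3 |

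At 20 per arm, per-outcome power goes from about 78% to between 81% and 85%. The chance of at least one success is identical under the two rules, because Holm's first step is the same 0.025 test.

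**5. What Holm gives up.** Suppose only one null is true. The false-positive rate for that outcome is 0.025 under the fixed rule. Under Holm with rho = 0 it is about 0.025 + 0.78 × (0.05 − 0.025) = 0.0445, where 0.78 is the power for the other outcome. It is lower at higher correlations (0.038 at rho = 0.9). About 0.04 is a fair summary, and it stays within 0.05.

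**The case against.** **The rule is not an error.** The 0.025 level is the same in the Abstract, the Sample size calculation and Statistical analyses, and the planned size follows from it. A reader might infer that the multiplicity adjustment is wrong or that the trial misses its stated power. The documents support neither. Planned power is 80% per outcome, and the normal formula gives 81% for each at 20 completers. This part of the objection stands in full.

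**Success on both outcomes is not a stated criterion.** The plan powers each outcome separately, and hypothesis 1 names both without requiring both. A reader might infer co-primary outcomes that must both succeed. The documents do not say so, and under that reading each could be tested at 0.05 with no adjustment, so neither Bonferroni nor Holm would be needed. The chance of supporting both is a reasonable yardstick for a hypothesis that names both, but no more than that.

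**Holm is not free.** It would be too strong to say that the fixed rule buys no error control at all. That is true family-wise, but the fixed rule protects each single outcome more tightly (0.025 against about 0.04 when only that null is true). Bonferroni also has matching intervals. Under Holm, a 97.5% interval includes zero whenever the second p-value lies between 0.025 and 0.05, which is where Holm changes the decision. Both points stand and belong in the fix.

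**Timing.** Recruitment was under way at submission (Trial status), participants know their group (Blinding), and the principal investigator can see the allocation sequence (Randomisation). Relaxing a published threshold mid-trial therefore needs a clear, dated lock. This limits how the change is made but does not rule it out.

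**Conclusion.** The fixed 0.025 rule is valid but avoidably inefficient. Holm's procedure keeps the two-sided family-wise error at 0.05 under any correlation, never rejects less, and needs no further patients or measurements.

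The gain in the chance of supporting both outcomes is about 7 to 12 points at the planned 20 completers per arm. A single figure such as 10 points should not be quoted without its conditions. Twenty completers means losing 10 of 30 (33%) in each arm; with better retention the gain falls to about 5 to 9 points at 25 and 3 to 6 at 30. It also depends on the between-outcome correlation and on two-sided testing, both of which are assumptions here. If the stated effect sizes already include the baseline adjustment, per-outcome power at 20 per arm is about 70% and the gain is 8 to 13 points, so the conclusion is the same.

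This is a worthwhile improvement and not a correction.

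**What to change.** Replace the sentence on the 0.025 level under Statistical analyses, and align the matching text in the Abstract, with:

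> The two primary outcomes are tested by Holm's procedure at family-wise two-sided 0.05: the smaller p-value at 0.025 and, if significant, the larger at 0.05.

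- Leave the sample size on 0.025.
- Fix and date the change before any outcome data are analysed by group, and notify the registry and the ethics committee as the Ethics section provides.
- For an outcome tested at 0.05, report the 95% interval, labelled as not simultaneous, alongside the Holm decision or the Holm-adjusted p-value. A 97.5% interval alone would appear to contradict the decision.
- State that the false-positive rate for one outcome can rise from 0.025 to about 0.04 when only its null is true.

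The cost is a short text change, the two notifications and slightly less simple interval reporting. No patients, visits or assessments are added.

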### Adverse events

The occurrence of any adverse events directly related to the procedures involved in this protocol will be collected during all testing visits. Participants randomised to the Ex + SED group will also be asked about the occurrence of adverse events resulting from the intervention prior to each exercise training session. Any untoward medical occurrence in a participant that may have a causal relationship with the intervention will be reported as an adverse event. A serious adverse event will be defined as any life-threatening, hospitalisation, disability or death that occurs because of an incident within two hours of completing an exercise session. Hospitalisations and deaths related to disease progression will not be reported as adverse events given the complex treatment and complications that are often associated with allo-SCT.

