### Transplant outcomes

Additional transplant-related outcomes will be recorded from Alfred Health patient medical records including the duration of hospital stay during the transplant procedure, time to engraftment, GVHD prophylaxis, development and severity, steroid use, and other relevant medications and/or complications (including rehospitalisation).

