### Data management

A unique study code will be assigned to all participants to ensure the confidentiality of their data is maintained. The secure online data management system REDCap (REDCap, Vanderbilt University, Nashville, USA) will be utilised to store all data and this will only be accessible to members of the study team. All data entered electronically will be double-checked for accuracy. Due to the low risks associated with the exercise components of the intervention, there will not be a formal data monitoring committee for this study. However, the study team will meet monthly to review study progress and data will be checked at regular intervals throughout the study.

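### The serious adverse event definition is tied to a two-hour post-exercise window and event enquiry differs by arm, so reported adverse events cannot be validly compared between arms

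*Protocol article*

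**What the plan says.** The Adverse events section of the protocol article contains four rules that bear on this point.

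- Collection not restricted by arm: "The occurrence of any adverse events directly related to the procedures involved in this protocol will be collected during all testing visits".
- An addition for one arm, before each training session: "Participants randomised to the Ex + SED group will also be asked about the occurrence of adverse events resulting from the intervention".
- The ordinary adverse event definition, which has no time window but is linked to the intervention: "Any untoward medical occurrence in a participant that may have a causal relationship with the intervention will be reported as an adverse event".
- The serious adverse event definition, which requires both a serious outcome and a particular cause and time, counted from the end of a session: "A serious adverse event will be defined as any life-threatening, hospitalisation, disability or death that occurs because of an incident within two hours".

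The section also sets one exclusion: "Hospitalisations and deaths related to disease progression will not be reported as adverse events".

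Three other sections matter. Usual care control group says that this arm receives no exercise support but is visited by the study coordinator twice a week in both phases. Transplant outcomes lists items taken from medical records without restriction by arm, among them length of stay, graft-versus-host disease and "other relevant medications and/or complications (including rehospitalisation". Data management says that "there will not be a formal data monitoring committee for this study", citing the low risk of the exercise components, and provides for monthly study team meetings.

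**The concern.** Seriousness normally describes the outcome of an event. When it happened relative to treatment, and whether treatment caused it, are separate questions. Here all three are folded into one definition, and the timing element refers to something that only one arm has. The count of serious adverse events in usual care is therefore fixed at zero before any data are collected. In the exercise arm the count leaves out some related events that are serious by any ordinary meaning.

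The enquiry rules add a second asymmetry. The exercise arm is asked often, about events resulting from the intervention. Usual care is asked rarely, about events resulting from study procedures. The two counts measure different things with different intensity.

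At stake is the trial's safety statement. The Safety precautions section describes patients with pancytopenia and possible haemodynamic instability, and the programme includes high-intensity intervals. The article expects its results to inform exercise guidelines for this population. A table of adverse events by arm built on these rules would make non-serious events look more frequent under exercise, and its serious-event rows could not be compared at all.

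**Working it through.** The article gives no safety figure to reproduce. The check has two parts: what each rule classifies, and how often each arm is asked.

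**Classification.** The table takes an event with a serious outcome and places it by its initiating incident, on the literal wording.

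| Initiating incident | Ex + SED | Usual care |
|---|---|---|
| During a session | Not clearly within the window; adverse event if possibly related | No session, so cannot be a serious adverse event |
| Up to two hours after a session ends | Serious adverse event | As above |
| More than two hours after a session | At most an ordinary adverse event, if possibly related | As above |
| During or after one of the ten daily activity breaks | Unclear whether a break counts as a session; the article describes breaks as separate from the thrice-weekly programme | No breaks prescribed |
| Treatment complication not thought related to the intervention | Not an adverse event; may appear in the records | Same |
| Hospitalisation or death related to disease progression | Excluded from adverse event reporting | Same |

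The two-hour limit attaches to the incident and not to the outcome. A death days later still qualifies if its cause arose in the window. What drops out of the serious category is related harm whose cause arose outside it.

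**Enquiry points after randomisation.** Inputs:

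- Three sessions a week for an inpatient phase of about 4 weeks, all supervised.
- Three sessions a week for 12 outpatient weeks, two of them supervised.
- Testing visits at baseline, about 1 week after discharge, and 12 weeks after discharge. Randomisation follows baseline, so 2 visits remain.

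The counts are:

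- Ex + SED, all sessions: 3 × (4 + 12) + 2 = 48 + 2 = 50.
- Ex + SED, supervised sessions only: 3 × 4 + 2 × 12 + 2 = 36 + 2 = 38. This is the safer count, since nobody is described as present before a home session.
- Usual care: 0 + 2 = 2.

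The ratio is 38/2 = 19 to 50/2 = 25. The Background section puts confinement at about 3 to 5 weeks. Over that range the counts are 47 to 53 for all sessions (3 × 15 + 2 to 3 × 17 + 2) and 35 to 41 for supervised sessions (9 + 24 + 2 to 15 + 24 + 2), still against 2.

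Recall periods differ as well. Baseline is about 2 weeks before admission, so the first enquiry in usual care comes about 2 + 4 + 1 = 7 weeks after baseline, and the next about 12 − 1 = 11 weeks later. The exercise arm is asked at intervals of days.

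**Scope.** At testing visits the question is about study procedures. The ordinary adverse event definition requires a possible link to the intervention, which usual care does not receive. Very little that happens in usual care can therefore qualify as an adverse event.

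**The case against.** The strongest reply is that harm is recorded elsewhere, and much of it stands. The ordinary adverse event definition has no time limit, so a late related event is still reportable and loses only the serious label. Testing visits cover both arms. Rehospitalisation, complications and graft-versus-host disease come from records without restriction by arm and can be compared. The article also describes pre-exercise contraindications, consultation with the haematologist and monthly team review. A between-arm safety comparison is not among its stated aims.

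Four stronger readings are tempting, and the article does not support them.

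- A reader might infer that the trial cannot detect or compare harm. The untimed adverse event definition and the record extraction contradict that.
- A reader might infer that excess deaths or readmissions under exercise would not show. Readmissions are in the extracted records. Deaths are not named in that list, but the Participant withdrawals section recognises deceased participants and keeps their data. The gap is in adverse event reporting.
- A reader might infer that causality is judged by staff who know the allocation. The article names no assessor.
- A reader might compute that the window covers 48 × 2 = 96 of 16 × 168 = 2,688 hours, or 3.6% of follow-up, and take this as the share of harm captured. It is a share of clock time. Acute exertional risk is not spread evenly over the week, so the figure says nothing about how many related events are missed.

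It may also be said that safety reporting detail belongs in the full protocol. That would answer a missing definition. Here the definition is stated, and the difficulty follows from its wording.

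**Conclusion.** The concern holds in a limited form. The serious adverse event definition makes a zero in usual care automatic and denies the serious label to related events that start during a session or later than two hours after one. Enquiry differs in frequency, about 38 to 50 points against 2, and in scope. Reported adverse and serious adverse events therefore cannot be validly compared between arms. A report of no serious adverse events in the exercise arm would mean only that none arose from an incident in the window.

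The counts assume a four-week inpatient phase, delivery of all prescribed sessions, and activity breaks not counted as sessions. The structural zero in usual care needs none of these. The statement about incidents during a session rests on reading the wording literally; the authors may have meant to include them, but the text does not say so. No primary or secondary efficacy conclusion is affected.

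**What to change.** Change the Adverse events section in four ways.

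1. Define a serious adverse event by outcome alone (death, life-threatening event, unplanned or prolonged hospitalisation, disability), in both arms, from randomisation to the 12-week test. Prolongation matters because every participant is already in hospital in Phase 1.
2. Record relatedness to the intervention, and timing relative to a session (during, within two hours after, later, or not applicable), as separate fields. The present window survives as a descriptor.
3. Ask both arms the same questions on a matched schedule. The twice-weekly usual-care visits give about 2 × 16 = 32 contacts over 16 weeks, and the exercise arm has at least two supervised sessions every week. Answers from additional pre-session questions should be kept out of the between-arm table.
4. Tabulate deaths, rehospitalisations and serious events by arm from the records already being extracted, adding death as a named item and including events attributed to disease progression, with the attribution shown.

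The cost is a wording amendment, a modest extension of the record extraction, and more events to log and review in a population with many complications. Recruitment had begun when the article was submitted. Serious events can be recovered from records for participants already enrolled, but matched questioning can start only from the amendment, so non-serious events before it should be reported descriptively and not compared. None of this alters any exercise or clinical rule.
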